**Protocol Précis**

Globally the estimated number of children living with HIV is 3 million. In Vietnam there are about 7100 children diagnosed with HIV, and 5000 are on treatment. Generally children with HIV are diagnosed late. The estimated average age at HIV diagnosis in the National Pediatric Hospitals is 3 years, and by this time the children are often severely immune-compromised. Children with HIV on ART have about twice the rate of virological treatment failure compared to adults. A large meta-analysis of pooled data from HIV-infected children after 12 months of ART showed that virological treatment failure rate is 30%; among those 13,7% had immunological failure. The consequences of treatment failure is greater in children as antiretroviral options for children are much more limited. The impact of this is further compounded for HIV-infected children in resource-poor settings where access to viral load monitoring is scare, and virological treatment failure is detected late, often long after they have experienced immunological and/or clinical failure. Prolonged treatment of non-suppressive therapy leads to development of accumulated drug resistance mutations and replication of multi-drug resistance HIV species, which further limit future therapeutic choices for children in resource poor settings. Many children live in difficult family situations with drug addiction and/or single mothers who are themselves infected with HIV. The lack of a structured support system of caretakers is probably the single most important factor driving poor treatment adherence in children. Several cross-sectional studies have shown a clear relationship between poor adherence and resistance development. There is great need to develop low cost and sustainable interventions that can be implemented in developing countries to improve adherence and long-term treatment outcome in children on ART.

**Synopsis**

**Title:** A randomized controlled trial to assess the impact of peer support to children and adolescents with HIV receiving antiretroviral therapy (ART) with virological treatment failure as primary endpoint

**Primary Objectives:** To study the impact of peer support to care takers of children with HIV receiving ART vs conventional care on rates and time to virological treatment failure and /or death and/or AIDS-associated events (clinical treatment failure) up to 24 month using a randomized controlled trial (RCT) design comparing enhanced treatment support (ETS) and conventional treatment (CT).

**Secondary Objectives:**

1. To compare the rate of and time to virological treatment failure (primary endpoint) immunological failure (secondary endpoint) /death/AIDS-associated events (tertiary endpoint) between the intervention and control group
2. To compare the rate of ART adherence between the intervention and control group
3. To compare the rate of acquiring OI’s, drug adverse effect, physical development, drug resistance between the intervention and control group.
4. To asses quality of life in intervention and control group before and after intervention
5. To assess cost effectiveness of peer support comparing to conventional care

**Study Designs:**

Randomized controlled trial, multi-center study

Randomization will be 1:1 and stratified by center and ART status at enrolment stratified according to naïve vs. on ART treatment.

**Study Regions:**

- Hanoi and Ho Chi Minh city

**Study Size:**  Planned enrollment of a total of 540 HIV positive children 10-16 years of age, on ART and randomize to either Enhanced Treatment Support (ETS) or Conventional Treatment (CT).

**Study Duration:** Study enrollment at the second quarter of 2019 and the study will be completed when all patients have completed follow up during 24 months.

**Study Population:**

**Inclusion Criteria:**

- Continuously followed up by Out Patient Clinic (OPC).
- Age from 10 to 16 years of age (based on date of birth)

**Exclusion Criteria:**

(any of the following):

- Being referred from other sites for temporarily follow-up at site study.
- Institutionalized patients (e.g. orphanage)

**Sample size:**

WHO sample formula for the intervention study, comparing to 2 proportions

We assume the possibility of treatment failure of 15% in the control arm and 10% in the intervention arm after 2 years of follow-up. With 80% power and a test at the two-sided 5% significance level, 10% losses of follow-up, approximately 540 patients are required **(260 per group)** into the trial.

**Enrollment:** All patients aged 10-18 years meeting the inclusion criteria are eligible at the study sites will be enrolled.

**Randomization:** The patients are randomized in the intervention or control group the first time of the intervention. E.g. all patients that attend the examination at a specific weekday will be included in intervention group other week day will be the control group. The peer group meetings will then be organized according to the day of examination where each group contain about 15 patients. Patients can/will not know which day is which until they come to avoid bias. Written consent will be done.

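### The planned 540 patients give about 42% power at best for 15% versus 10% failure, not the stated 80%; the protocol's own inputs need about 686 per group

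*Protocol*

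**What the plan says.** The Sample size paragraph in the Synopsis names its method: "WHO sample formula for the intervention study, comparing to 2 proportions". It gives the effect: "We assume the possibility of treatment failure of 15% in the control arm and 10% in the intervention arm after 2 years of follow-up". It then concludes: "With 80% power and a test at the two-sided 5% significance level, 10% losses of follow-up, approximately 540 patients are required", adding in brackets that this is 260 per group.

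The Study Size entry confirms that 540 is the whole trial and not one arm: "Planned enrollment of a total of 540 HIV positive children 10-16 years of age". Study Designs gives 1:1 allocation.

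Two other places bear on how losses enter the calculation. Indicators for Evaluation (the text and item 12 of the table) analyses patients lost to follow-up as deaths. Statistical Considerations counts death and loss to follow-up as failure in the survival analysis and specifies intention to treat.

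**The concern.** Every input needed to check the sample size is stated, and the result does not follow from them. A difference of 5 percentage points around a failure rate of 12.5% needs far more than 270 patients per arm for 80% power.

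The stated chance of missing a true benefit of the assumed size is 20%. With 540 patients it is close to 60% at best. A null result could then be read as evidence that peer support does not work, when the trial was more likely than not to miss the benefit it was planned for. The ethics committee and the data and safety monitoring board would be relying on a wrong figure. Indicators for Evaluation also makes the cost-effectiveness assessment conditional on a significant difference, so low power puts that secondary objective at risk too.

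**Working it through.** **Inputs, all from the Protocol.** Control rate p1 = 0.15 and intervention rate p2 = 0.10; two-sided 5% (z = 1.96); 80% power (z = 0.8416); 10% loss (all from Sample size); 1:1 allocation (Study Designs); total 540 (Sample size and Study Size). The mean rate is 0.125.

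**1. Attempt to reproduce 540.** Pooled two-proportion formula, per group:

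n = [1.96 × √(2 × 0.125 × 0.875) + 0.8416 × √(0.15 × 0.85 + 0.10 × 0.90)]² / 0.05²

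= [1.96 × 0.4677 + 0.8416 × 0.4664]² / 0.0025 = 1.3092² / 0.0025 = 685.6, so 686 per group and 1,372 in total.

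After 10% loss: 685.6 / 0.90 = 761.8, so 762 per group and 1,524 in total. The stated figure is not reproduced; 540 / 1,524 is about 35% of the requirement.

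**2. Other formulas, same inputs, two-sided, before loss.**

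| Method | Requirement |
|---|---|
| Unpooled variance | 683 per group |
| Arcsine | 681 per group |
| Continuity-corrected | 726 per group |
| Log-rank, Schoenfeld | 168 events, about 1,344 in total |
| Log-rank, Freedman | 173 events, about 1,384 in total |

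The log-rank rows use a hazard ratio of ln 0.90 / ln 0.85 = 0.648 and an average event rate of 12.5%. No variant comes near 540 in total.

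**3. Power at the planned size.** With n per arm:

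power = Φ{[0.05 − 1.96 × √(0.21875 / n)] / √(0.2175 / n)}

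| Per arm | What it represents | Power |
|---|---|---|
| 270 | 540 in total, all analysed | 41.9% |
| 260 | 520 in total, all analysed | 40.6% |
| 243 | 270 less 10% | 38.4% |
| 234 | 260 less 10% | 37.2% |

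For 270: [0.05 − 1.96 × 0.02846] / 0.02838 = −0.204, and Φ(−0.204) = 0.419. On the log-rank scale, 540 × 0.125 = 67.5 expected events give 42.9%, so the time-to-event endpoint does not change the picture.

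**4. Allowing for the loss-as-failure rule.** Lost patients stay in the analysis as failures, so 270 per arm is the relevant size. There are two readings of the assumed rates.

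- *15% and 10% already include losses.* Power is 41.9%. With 270 per arm and 15% in control, 80% power is reached only when the intervention rate is about 7.4% (power 80.1%).
- *Losses come on top.* For illustration, assume 10% are lost in each arm and the stated rates hold among the rest. Control: 0.10 + 0.90 × 0.15 = 23.5%. Intervention: 0.10 + 0.90 × 0.10 = 19.0%. The difference shrinks to 4.5 points and the variance rises. Power at 270 per arm is 24.7%, and 80% power would need about 1,297 per group. If the 10% are simply added to each rate (25% versus 20%), power is 28.4%.

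**5. Internal total.** 2 × 260 = 520, whereas 540 / 2 = 270.

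**The case against.** The strongest objection is to the 38% figure. A reader might infer that 38% is the trial's power, because Sample size allows for 10% losses and 540 less 10% leaves 486. The documents do not support that: lost patients are analysed as failures, so no reduced set of 486 exists in the planned analysis. This objection stands. The 38% shows only what follows if losses are removed, and the 762 per group follows the Sample size wording rather than the loss-as-failure analysis. The objection does not help the stated 540, because keeping everyone gives 42% at best.

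A reader might also infer that 540 is a per-group figure from a one-sided test: the pooled formula at one-sided 5% gives 540 per group before loss. That is conjecture. The protocol says two-sided, says losses are allowed for, and calls 540 a total. The error does not depend on its origin.

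The mismatch between 260 and 270 per group is minor. The text says approximately, and the difference moves power by about one point. It needs correcting for consistency but adds little to the main error.

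The formula itself is named but not shown, and the main analysis will be a regression model with patient characteristics. Neither could plausibly close a gap from about 42% to 80%.

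**Conclusion.** The point holds. On the protocol's own assumptions the sample size is wrong by a factor of about 2.5 before loss (1,372 / 540) and about 2.8 after it (1,524 / 540). Power for 15% versus 10% at two-sided 5% is about 42% if the assumed rates already include losses, and about 25% in the illustration where 10% per arm are lost on top. The first figure uses only numbers in the protocol; the second rests on equal 10% loss in both arms, with the stated rates holding among those retained.

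A reader might conclude that the trial has to be enlarged. The documents do not settle that. They show that the 80% claim is false for the planned enrolment; they do not show whether more patients could be recruited or whether a larger effect could be justified.

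**What to change.** Amend Sample size, and keep Study Size consistent with it:

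- Keep 540 as the planned total and give 270 per group throughout.
- Say whether 15% and 10% already include patients lost to follow-up and counted as failures.
- Replace the 80% claim accordingly. If losses are included: about 42% power for 15% versus 10%, and 80% power only for a fall from 15% to about 7.4%. If losses come on top: state the assumed loss per arm and the resulting power (about 25% with 10% in each arm).
- Add that a non-significant result does not rule out a 5-point benefit.

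The cost is a text amendment with a less favourable power statement. No extra patients, visits or procedures are needed. Should the sponsor prefer to enlarge the trial or to justify another effect size, the calculation should be redone on the same loss-as-failure basis.

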## Peer Support Intervention “Enhanced Treatment Support (ETC)”

1. Caretakers of children and adolescents with HIV on ART will be supported to achieve better adherence through peer support groups and phone follow-up, with an option for home visits or to return to support groups later if necessary. The activities will be organized by peer supporters, HIV-infected young adults selected by peers who will undergo a series of training, including medication adherence and counselling skills.

The support will include

1. Peer group support:

- Home visit
- Telephone support
- Focus group discussion

1. More support during medical visit
2. Peer group meetings with about 15 children and adolescents and their supporters arranged according to age groups of children and adolescents 10 – 12 years , 16 years as well as according to location, e.g. one group per age group per district. Each peer group meeting will be arranged by two peer supporters, one that takes care of the caretakers and the other the children. Each peer group meeting should have a generic part in relation to adherence where each caretaker can bring up problems and discuss them with the supporter and other group members. At each meeting some new information will be provided, either from the supporter or by some invited person arranged by the project, according to a training program.
3. The supporters will also have at least one telephone contact with the caretakes per week, if needed more, to assess the condition of the child/adolescent. To those who cannot make a particular support group session phone calls or home visits (if consent is given) are made. Follow up phone calls will be made to those whom the case manager identifies to need more support.
4. The meeting will be arranged in relation to the treatment day, e.g. at ND1 on Mondays and Wednesdays, when the patients are available at the clinic.
5. The peer-supporters will be trained by the research team and given training material to share with their Peer support groups. The training will include: Basic HIV knowledge review, Nutrition and HIV, Opportunistic Infections, Mental health, Antiretroviral Therapy and Adherence, Medication Adherence Support, Role of the peer-supporters, Setting boundaries and working as part of multidisciplinary team, Disclosure, Outreach overview, Confidentiality, Counseling skills, Study forms (CRF) and reports

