**Appendix 1A: Study Flow Diagram**

**Consent**

**Inclusion Criteria**

**Exclusion Criteria**

**Baseline assessment**

**Treatment Randomization (1:1)**

**EST**

**CT**

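### The protocol declares stratified 1:1 randomisation, but the only allocation method it describes is by clinic weekday, with no concealment from staff and no control of ART status or the 1:1 ratio

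*Protocol*

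**What the plan says.** The Study Designs section of the synopsis describes a "Randomized controlled trial, multi-center study" and adds: "Randomization will be 1:1 and stratified by center and ART status at enrolment", the ART strata being treatment-naïve and already treated. The flow diagram in Appendix 1A lists consent, eligibility and baseline assessment, then "Treatment Randomization (1:1").

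The method stands in the Randomization paragraph under Sample size. It says that patients are randomised at the first intervention contact and then gives, as an example, that "all patients that attend the examination at a specific weekday will be included in intervention group other week day will be the control group". Two sentences build on this: "The peer group meetings will then be organized according to the day of examination where each group contain about 15 patients" and "Patients can/will not know which day is which until they come to avoid bias".

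The Sample size section compares two proportions (15% against 10%). Statistical Considerations plans regression on a group indicator and patient characteristics. Neither mentions the clinic day as a unit of allocation.

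**The concern.** If the weekday sets the arm, chance does not. The day on which a child attends may go with the treating clinician, distance to the clinic, school hours or the caretaker's work. Each of these may plausibly affect adherence, which is the route by which peer support is meant to act. A difference between arms could then reflect who comes on which day.

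A fixed day rule is also predictable. Once a day is tied to an arm, anyone who books, recruits or takes consent can foresee the arm of the next child. Finally, the rule allocates days at sites, while the sample size and the analysis treat children as independently allocated.

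**Working it through.** **Comparing the sections.** The allocation text contains no figure to reproduce, so the check is whether the weekday rule can deliver what Study Designs and Appendix 1A promise.

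- *Random assignment.* No random sequence is described, and no random draw of days to arms. The rule as written is systematic.
- *Concealment.* The one safeguard concerns patients before arrival. Nothing covers staff, and no central or sealed list is mentioned.
- *Balance by centre.* Possible, provided that each centre has both kinds of day.
- *Balance by ART status.* Not controllable, because everyone attending on a given day gets the same arm.
- *1:1 ratio.* Depends on how many children attend on each kind of day.
- *Timing.* Appendix 1A places randomisation after consent and baseline. Under the weekday rule, attendance itself fixes the arm.

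**Illustration 1: a difference between weekday populations.** Inputs from the protocol: 540 children, hence 270 per arm, or 270 × 0.90 = 243 after 10% loss; two-sided 5% test. Assumed: no effect of peer support, and failure rates p1 and p2 on the two kinds of day. The chance of a significant result favouring the lower-rate day is

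Φ[(p1 − p2 − 1.96·√(2·p̄(1 − p̄)/n)) / √((p1(1 − p1) + p2(1 − p2))/n)], where p̄ is the mean of p1 and p2.

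For 15% against 12% with n = 270, the two standard errors are 0.0294 and 0.0294, so Φ[(0.030 − 0.0576)/0.0294] = Φ(−0.94) = 0.173.

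| Assumed rates by day | n = 243 | n = 270 |
|---|---|---|
| 15% v 14% | 5.0% | 5.2% |
| 15% v 13% | 9.3% | 9.8% |
| 15% v 12% | 16.0% | 17.3% |

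The nominal value in that direction is 2.5%.

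**Illustration 2: clustering by site and weekday.** Assumed: 8, 12 or 20 site-weekday units, and an intracluster correlation (ICC) of 0.01 or 0.05. None of these is in the protocol. With m = 540/units, the design effect is DE = 1 + (m − 1)·ICC, and the true type I error of a nominal 5% test is 2·[1 − Φ(1.96/√DE)].

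| Units | m | DE, ICC 0.01 | Type I error | DE, ICC 0.05 | Type I error |
|---|---|---|---|---|---|
| 8 | 67.5 | 1.67 | 12.9% | 4.33 | 34.6% |
| 12 | 45 | 1.44 | 10.2% | 3.20 | 27.3% |
| 20 | 27 | 1.26 | 8.1% | 2.30 | 19.6% |

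The formula loads all between-unit variation on the arm contrast. If each centre has both kinds of day and the analysis adjusts for centre, only the variation between days within a centre counts, and that may be smaller.

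**The case against.** The strongest reply is that the weekday is only an example and that the preceding sentence says patients are randomised. That lowers certainty about what was intended. It does not remove the contradiction, because no other method is given and the next sentences rely on the day rule. If the example is not the method, the protocol describes no method at all.

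Some stronger readings are tempting but are not supported:

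- *The trial is simply not randomised.* The protocol does not say how days are matched to arms. Days drawn at random within centre would make a cluster-randomised trial with few clusters, although the protocol does not declare one.
- *Stratification is impossible.* This holds for ART status, not for centre.
- *There is no protection against foreknowledge.* There is a patient-side safeguard. It is insufficient because it leaves out staff.
- *The protocol shows that staff know the intervention days.* The sentence "The meeting will be arranged in relation to the treatment day, e.g. at ND1 on Mondays and Wednesdays, when the patients are available at the", in the Peer Support Intervention section, does not say that both are intervention days; they may just be that clinic's attendance days. Foreknowledge by staff is a reasonable inference from a fixed rule, not a stated fact.

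The description of the study size as children "on ART and randomize to either Enhanced Treatment Support (ETS) or Conventional Treatment (CT") may seem to empty the naïve stratum. The inclusion criteria do not require ART, and the Appendix 1B flow chart makes adherence assessment conditional on already being treated. That is a separate inconsistency, and this point does not depend on it.

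Separate days also have a practical merit: they keep the arms apart. Any replacement should preserve that where it can.

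**Conclusion.** The point stands and must be fixed. Study Designs and Appendix 1A cannot be reconciled with the only allocation method described. Followed as written, that method is quasi-random, predictable to staff, and unable to control ART status or the 1:1 ratio. A result could not be cleanly attributed to peer support.

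These conclusions come from the text alone. The size of the damage does not. The 5% to 17% range in the first illustration rests on assumed differences between days of 1 to 3 percentage points, and the protocol gives no evidence that such differences exist. The 8-13% type I error (ICC 0.01), or 20-35% (ICC 0.05), rests wholly on assumed unit counts and correlations. A reader might take these as estimates of the trial's actual error rate; they show only that modest departures would matter.

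**What to change.** Delete the weekday rule from the Randomization paragraph. Allocate each child after written consent and baseline assessment from a concealed, computer-generated permuted-block list held centrally, for example through the online CRF that Data Management already foresees. Stratify by centre and ART status, as Study Designs states. Then book later visits so that ETS children attend on peer-meeting days and CT children on other days where possible.

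The cost is an allocation list, rebooking work and some possible contact between arms. That contact could recur beyond the first visit if CT children go on attending on meeting days, which is why both arms need booking.

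If weekday allocation has already been used, describe the study as quasi-randomised, or as cluster-randomised if days were drawn at random to arms. Adjust for centre and baseline factors, account for site-weekday in the standard errors, and acknowledge the loss of precision, which could be substantial with few units. Adjustment would not restore the protection that concealed randomisation gives.

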## Peer Support Intervention “Enhanced Treatment Support (ETC)”

1. Caretakers of children and adolescents with HIV on ART will be supported to achieve better adherence through peer support groups and phone follow-up, with an option for home visits or to return to support groups later if necessary. The activities will be organized by peer supporters, HIV-infected young adults selected by peers who will undergo a series of training, including medication adherence and counselling skills.

The support will include

1. Peer group support:

- Home visit
- Telephone support
- Focus group discussion

1. More support during medical visit
2. Peer group meetings with about 15 children and adolescents and their supporters arranged according to age groups of children and adolescents 10 – 12 years , 16 years as well as according to location, e.g. one group per age group per district. Each peer group meeting will be arranged by two peer supporters, one that takes care of the caretakers and the other the children. Each peer group meeting should have a generic part in relation to adherence where each caretaker can bring up problems and discuss them with the supporter and other group members. At each meeting some new information will be provided, either from the supporter or by some invited person arranged by the project, according to a training program.
3. The supporters will also have at least one telephone contact with the caretakes per week, if needed more, to assess the condition of the child/adolescent. To those who cannot make a particular support group session phone calls or home visits (if consent is given) are made. Follow up phone calls will be made to those whom the case manager identifies to need more support.
4. The meeting will be arranged in relation to the treatment day, e.g. at ND1 on Mondays and Wednesdays, when the patients are available at the clinic.
5. The peer-supporters will be trained by the research team and given training material to share with their Peer support groups. The training will include: Basic HIV knowledge review, Nutrition and HIV, Opportunistic Infections, Mental health, Antiretroviral Therapy and Adherence, Medication Adherence Support, Role of the peer-supporters, Setting boundaries and working as part of multidisciplinary team, Disclosure, Outreach overview, Confidentiality, Counseling skills, Study forms (CRF) and reports
6. In ***CT*** ***control group*** the treatment will be supported according to the treatment guidelines. Both groups will receive treatment counseling and be followed through regular clinical check-ups, the drugs will be provided in a pre-packed dosage form for easy remembering and counting of the pills.

